### Sample size calculation

Sample size calculations were performed based on our primary outcome variable, the KOOS pain score, with a desired power of 80% and a significance level of 0.05 using the statistical software Stata version 11.2. Given the early stage of research concerning the effects and interactions of load reduction, and different OA subtypes on treatment outcome, we chose to only conduct sample size calculations on a repeated measures basis for within group comparisons. Based on the results of this trial, sample sizes may be expanded to increase statistical power in order to make comparisons between the control and KAM-R group.

The minimum perceptible clinical improvement and minimum detectible change in KOOS score has been reported to be about 13.4 points [33, 41]. Using a baseline KOOS pain score of 57.3 points [42] and a standard deviation of 15 points [41], to detect a minimal clinically important improvement of 13.4 points within each group, 20 participants are required in each group, or 40 total participants. To account for a potential dropout rate of 15%, we will recruit a minimum of 46 participants.

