### Primary outcome measures

The primary outcome measure in this study will be the KOOS pain score (0–100 points). This measure will allow us to identify the overall treatment effect of the wedged insole intervention over the 3-month follow-up period.

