#### Within group analyses

All data will be analyzed on an intention to treat basis. Changes from baseline to 3 months will be assessed within groups for ordinal data (UCLA score) using Wilcoxon Signed Rank test (α = 0.05). KOOS subsection scores and PASE scores will be compared between baseline and at 3 months using paired-samples t-tests (α = 0.05). KAMs, KAM impulse, varus thrust, and footwear comfort will be compared between the neutral shoe and assigned wedged insole condition at baseline for the KAM-R group using paired-samples t-tests (α = 0.05). All tests will be two-tailed, except in the case of KAMs and KAM impulse, where one-tailed tests will be used. The reason for this is that KAM reduction is strictly controlled in this study and so KAM and KAM impulse reductions are the only possible outcome.

A multivariable linear regression (α = 0.05) will also be conducted on the KAM-R group to evaluate whether KAM reduction, KAM impulse, varus thrust and footwear comfort can predict change in pain over 3 months. Covariates tested in these four models will include adiposity and Kellgren-Lawrence grade.

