#### Between group analyses

Ordinal data from UCLA scores and Kellgren-Lawrence grades will be compared at baseline and at 3 months (UCLA score only) between the control and KAM-R group using Mann–Whitney U tests (α = 0.05). KOOS subsection scores, PASE scores, KAMs, KAM impulse, varus thrust, adiposity, footwear comfort, and adherence will be compared at baseline between the KAM-R and control group using a MANOVA test (α = 0.05) with independent-samples t-tests for post-hoc analysis. Changes over 3 months will also be assessed between groups using a MANOVA (α = 0.05) with independent-samples t-tests for post-hoc analysis. All tests will be two-tailed, except in the case of KAMs and KAM impulse, where one-tailed tests will be used. The reason for this is that KAM reduction is strictly controlled in this study and so a reduction in KAMs and KAM impulse is the only possible outcome. It should be noted that all between group comparisons are exploratory analyses, as we may not be powered to detect any significant differences between groups.

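### The 20 per group labelled as a within-group sample size does not follow from the stated inputs as a paired calculation unless baseline and 3-month scores are uncorrelated, and 46 recruits do not quite cover 15% dropout

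*Protocol article*

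**What the plan says.** All references are to the protocol article.

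- *Sample size calculation* names the basis: "we chose to only conduct sample size calculations on a repeated measures basis for within group comparisons". The calculation was done "with a desired power of 80% and a significance level of 0.05 using the statistical software Stata version 11.2".
- The same section gives the inputs, "Using a baseline KOOS pain score of 57.3 points [42] and a standard deviation of 15 points [41"], and the result: "to detect a minimal clinically important improvement of 13.4 points within each group, 20 participants are required in each group, or 40 total participants". It does not say whether 15 is the SD of scores or of change, and it gives no correlation between baseline and 3 months.
- On attrition it says: "To account for a potential dropout rate of 15%, we will recruit a minimum of 46 participants".
- *Primary outcome measures*: "The primary outcome measure in this study will be the KOOS pain score". *Within group analyses* plans paired t-tests for it and settles the sidedness: "All tests will be two-tailed, except in the case of KAMs and KAM impulse, where one-tailed tests will be used".
- *Between group analyses* treats every comparison of the arms as exploratory, "as we may not be powered to detect any significant differences between groups".
- *Randomization* places allocation after the baseline laboratory and survey tests. *Blinding* places it before any data are collected and before the KAM results are known. Both sections exclude participants in whom neither insole lowers the KAM.

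**The concern.** The label and the number do not fit together. A paired design normally needs far fewer patients per group than a comparison of two independent groups with the same effect and SD, yet the figure given as paired is exactly what the two-group formula returns.

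This matters because the hypothesis in *Background* is comparative: greater improvement with the insole than in the control group. As written, a reader cannot tell what the trial is powered for. The within-group power is not the 80% that the text suggests, the between-arm power is never quantified, and the exploratory status of the randomised comparison is justified by a power statement with no figure behind it. The recruitment target built on this number also falls slightly short of its own dropout allowance.

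**Working it through.** **Inputs.** From *Sample size calculation*: difference 13.4, SD 15, alpha 0.05, power 80%, dropout 15%. Two-sided testing of KOOS comes from *Within group analyses*. The baseline mean of 57.3 does not enter a formula for an absolute difference. The correlation r between baseline and 3-month scores is not given, so it is varied below as an assumption.

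**1. Reproducing the stated 20.** Two independent means, per group:

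n = 2 × (1.960 + 0.842)² × 15² / 13.4² = 2 × 7.849 × 225 / 179.56 = 19.67, rounded up to **20**.

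This matches. Other settings of the same formula do not: one-sided 80% gives 16 and two-sided 90% gives 27. The exact t version gives 21.

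**2. The calculation that the text describes.** Paired, with 15 as the SD of change:

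n = 7.849 × 225 / 179.56 = 9.84, so **10** per group (12 by the noncentral t distribution).

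**3. When a paired calculation gives 20.** If 15 is the SD of scores, the SD of change is 15 × √(2(1 − r)). The paired formula returns 19.67 only when this equals 15 × √2 = 21.2, that is, at r = 0.

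**4. What 20 per group delivers** for 13.4 points, with 15 as the SD of scores (powers by t):

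| r | SD of change | Paired n, normal (t) | Paired power, n = 20 | Between-arm power on unadjusted change, 20 per arm |
|---|---|---|---|---|
| 0 | 21.2 | 20 (22) | 76.4% | 49.5% |
| 0.3 | 17.75 | 14 (16) | 89.3% | 64.3% |
| 0.5 | 15.0 | 10 (12) | 96.6% | 78.6% |
| 0.7 | 11.6 | 6 (9) | 99.8% | 94.4% |

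The row r = 0.5 is also the case in which 15 is itself the SD of change. If SD 15 applies to whatever is compared between arms, power at 20 per arm is 78.6% by t (80.6% by the normal formula).

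Paired power by t reaches 80% at n = 20 when the SD of change is 20.29. That corresponds to r = 1 − 20.29² / (2 × 225) = 0.085, or about 0.09.

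**5. Dropout.** 40 × 1.15 = 46, which is the stated target. Expected completers are 46 × 0.85 = 39.1. Keeping 40 needs 40 / 0.85 = 47.06, so 48 with equal arms (24 each). The loss that 46 can absorb is 6/46 = 13%.

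**6. KAM exclusions.** The article gives no rate and says only that such cases will be uncommon. If the 46 are counted before this exclusion, an assumed rate of 5% leaves 46 × 0.95 × 0.85 = 37.1 evaluable, and an assumed 15% leaves 46 × 0.85 × 0.85 = 33.2.

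**The case against.** **The stated power is a target, and it is met.** The text calls 80% the desired power. Twenty per group reaches it by paired t-test at any correlation above about 0.09, and by the normal formula even at zero. This stands: the within-group tests are not underpowered on the stated inputs, and the mismatch errs on the safe side.

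**The command that was run is not shown.** A reader might infer that the two-sample formula was certainly used by mistake. The document does not establish this, because a paired calculation with uncorrelated scores gives the same number. What can be said is that the label fits only under an assumption that the text does not state and that would remove the gain from repeated measures.

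**Is the trial in fact powered for the randomised comparison?** A reader might infer that it is, and that the caution in *Between group analyses* is wrong and should go. The documents do not support this, for four reasons:

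- The caution is only a hedge. No section claims that between-arm power is absent.
- The 13.4 points are stated as an improvement within each group. Power of about 79% needs that whole amount as a difference between arms.
- The section compares changes over 3 months. If 15 is the SD of scores, power at low correlation is well short of 80%. Citing higher power from a baseline-adjusted model would not help, because the planned analysis is MANOVA followed by t-tests.
- *Sample size calculation* gives the early stage of the research as its reason for sizing on within-group change. Correcting the arithmetic does not remove that choice.

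**The dropout shortfall is small.** It is about one completer, or two recruits against 48, and 46 is given as a minimum. This also stands, although the sentence remains arithmetically wrong.

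**Do the 46 count patients randomised after the KAM check?** A reader might assume so from *Randomization*, but *Blinding* says the opposite about the order of events.

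**Conclusion.** The concern holds as a mismatch between a number and its label. On the stated inputs the paired size is 10 to 12 per group if 15 is the SD of change. The stated 20 is the two-independent-sample size, or the paired size at zero correlation.

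The consequence for the within-group tests is benign: about 97% power if the SD of change is 15, and below 80% (76% by t) only when the correlation is near zero. The consequence for the randomised comparison is that its power is undeclared and cannot be fixed from the text. It is about 79% for a full 13.4-point difference if SD 15 applies to the quantity compared. If 15 is the SD of scores, it runs from 49.5% to 94% over correlations of 0 to 0.7. These correlations are assumptions.

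The dropout inflation is wrong by a small amount: 39.1 expected completers against 40. Whether exclusions for lack of KAM reduction reduce this further cannot be settled until the order of randomisation and baseline testing is made consistent.

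**What to change.** 1. In *Sample size calculation*, state the formula actually used and say whether 15 is the SD of scores or of change. If it is the SD of scores, give the assumed correlation.
2. In the same section, add the between-arm power at 20 evaluable per arm with its assumptions: about 79% (t) for a 13.4-point difference if SD 15 applies to the quantity compared; otherwise 49.5%, 64%, 79% and 94% at r = 0, 0.3, 0.5 and 0.7 for unadjusted change.
3. Keep the caution in *Between group analyses*, but tie it to those assumptions.
4. Either restate the tolerated dropout as 13% or set the target at 48 (24 per arm).
5. Say whether the target is counted before or after exclusion for no KAM reduction, and reconcile *Randomization* and *Blinding* on whether allocation precedes baseline testing.

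The cost is a rewording of these sections. No extra patients are needed if the dropout figure is restated, and two more recruits if the target becomes 48.

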**Methods/design:**

Forty-six patients with radiographically confirmed diagnosis medial knee OA will be recruited for this 3 month randomized controlled trial. Recruitment will be from Alberta and surrounding areas. Eligibility criteria include being between the ages of 40 and 85 years, have knee OA primarily localized to the medial tibiofemoral compartment, based on the American College of Rheumatology diagnostic criteria and be classified as having a Kellgren-Lawrence grade of 1 to 3. Patients will visit the laboratory at baseline for testing that includes dual x-ray absorptiometry, biomechanical testing, and surveys (KOOS, PASE activity scale, UCLA activity scale, comfort visual analog scale). At baseline, patients will be randomized to either a wedged insole group to reduce KAMs, or a waitlist control group where no intervention is provided. The survey tests will be repeated at 3 months, and response to wedged insoles over 3 months will be evaluated.

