## Methods

### Participant consent & ethical approval

Ethics approval for this study has been obtained from the University of Calgary Conjoint Health Research and Ethics Board (CHREB). In accordance with CHREB guidelines, written consent will be obtained from each individual prior to being enrolled in the study formally as a participant, and prior to any testing.

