### Randomization

Following the baseline laboratory and survey testing, participants will be randomized into one of two study arms: (1) a KAM-reduction experimental group (KAM-R), or (2) a waitlist control group. In the KAM-R group, participants will be given either a medial or lateral wedge insole (whichever insole reduces KAMs more for each individual participant) to put inside their own shoe and use for 3 months. In the waitlist control group, participants will be asked to continue using their own shoes for a period of 3 months, and following this will be provided with access to a wedged insole (whichever reduces KAMs more based on baseline data collection).

Participants will be randomized using a multi-block-randomization procedure into either the KAM-R or waitlist control group. Specifically, a separate block sequence will be used for males and females to ensure an even sex distribution across groups. A block size of 6 will be used for each, and the sequence will be determined from a random number generator.

The one exception to this block randomization procedure is that if neither wedged insole produces a KAM reduction, the participant will be excluded from the main study altogether. This scenario will not be common, as most people do experience a large change in KAMs with one of the two wedged insole types, but this strategy will ensure that all participants in the KAM-R and waitlist control groups are all biomechanically suitable for a wedged insole intervention. Thus, neither group will contain biomechanical non-responders to wedged insoles.

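### The target of 46 allows for 15% dropout but not for the planned removal of participants without a KAM reduction, and the article does not say whether the 46 is counted before or after that check

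*Protocol article*

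**What the plan says.** The Sample size calculation section of the protocol article sizes the trial on within-group change in KOOS pain: "to detect a minimal clinically important improvement of 13.4 points within each group, 20 participants are required in each group, or 40 total participants". It then makes one allowance for loss: "To account for a potential dropout rate of 15%, we will recruit a minimum of 46 participants". The abstract (Methods/design) gives the same number as people recruited and describes the baseline laboratory visit after that: "Forty-six patients with radiographically confirmed diagnosis medial knee OA will be recruited for this 3 month randomized controlled trial".

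The Randomization section adds a rule based on the baseline gait measurements: "if neither wedged insole produces a KAM reduction, the participant will be excluded from the main study altogether". It gives no rate and says only that the situation is expected to be uncommon. No replacement rule is stated.

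The article gives two orders of events. The Randomization section randomizes after baseline laboratory and survey testing. The Blinding section randomizes before any data are collected and checks the KAM result afterwards, so a participant who fails the check has already been allocated to an arm.

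**The concern.** Two planned losses lie between recruitment and analysis, dropout and failure of the KAM check, and the step from 40 to 46 covers only the first. If recruitment stops at 46 people who have not yet had the KAM check, both losses come out of the same 46, and the trial ends with fewer than the 20 per group that its own calculation requires. On the Blinding section's order, the removals come directly out of the randomized arms. In a trial of this size, a few people are a noticeable share of each group.

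**Working it through.** **Inputs from the article.** Difference 13.4 points, SD 15, 80% power, significance level 0.05, 20 per group, 15% dropout and 46 recruits (Sample size calculation); two-tailed paired t-tests for KOOS scores (Within group analyses). The KAM exclusion share *e* is not given, so I assume 2% to 15%.

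**Reproducing the plan's figures.**
- n per group = 2 × [15 × (1.960 + 0.842) / 13.4]² = 19.67, rounded up to 20. For a paired comparison, this equals a normal-approximation formula with an SD of change of 15 × √2 = 21.2, that is, zero correlation between baseline and 3 months.
- If 15 were itself the SD of change, the same formula would give 9.8, or 10 per group. The stated 20 therefore rests on the first form.
- Recruitment: 40 × 1.15 = 46, the stated figure.

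**Slack in the target.** To keep 40 out of 46, all losses together must not exceed 6/46 = 13.0%. The plan's own 15% dropout already exceeds this: 46 × 0.85 = 39.1, or 19.55 per group. Dividing instead, 40/0.85 = 47.1, which is 48 with equal arms.

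**Adding the KAM check, if the 46 is counted before it.** Analysable = 46 × (1 − *e*) × 0.85. The KAM share is 39.1 minus that number. Recruits needed = 40 / [(1 − *e*) × 0.85], rounded up.

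| Assumed *e* | Analysable | Per group | Lost to KAM check | Recruits needed for 40 |
|---|---|---|---|---|
| 0% | 39.1 | 19.6 | 0 | 48 |
| 2% | 38.3 | 19.2 | 0.8 | 49 |
| 5% | 37.1 | 18.6 | 2.0 | 50 |
| 10% | 35.2 | 17.6 | 3.9 | 53 |
| 15% | 33.2 | 16.6 | 5.9 | 56 |

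The recruit number is rounded up to the next even number where equal arms are wanted; the 0% row already is.

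**Power.** On the normal formula that reproduces 20 per group, power is 80.6% at 20 per group and 79.8% after dropout alone. At the four exclusion rates it is 79.0%, 77.7%, 75.5% and 73.1%.

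The planned test is a paired t-test, whose SD of change is 15 × √[2(1 − r)], with r the baseline to 3-month correlation. The article gives no r, so these values are assumptions:

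| r | 20 per group | *e* = 5% | *e* = 10% | *e* = 15% |
|---|---|---|---|---|
| 0 | 76% | 73% | 70% | 68% |
| 0.3 | 89% | 87% | 85% | 82% |
| 0.5 | 97% | 95% | 94% | 93% |

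At r of about 0.3 or more, power stays above 80% throughout this range of exclusion rates.

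**The case against.** The strongest reply is that the article never says the 46 is counted before the KAM check. In the Randomization section, the check works like a screening criterion: testing comes first, those who fail leave the main study, and both groups then hold only biomechanically suitable people. Screening failures do not normally count toward a target. This reading is open, and the concern is conditional for that reason. It conflicts with the Blinding section, however, and even on this reading 46 yields 39.1 after dropout.

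A reader might take the consent section as proof that enrolment precedes testing. It does not say so: "written consent will be obtained from each individual prior to being enrolled in the study formally as a participant". The sentence goes on to place consent before testing as well. It puts consent ahead of both events and does not order enrolment against testing.

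The 46 is also a minimum, so recruiting more is allowed, and a replacement rule may stand in the full protocol. Both points are fair. They limit the claim, but they do not supply an allowance that the stated calculation leaves out.

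The size rests on an assumed rate. At 2%, the check costs less than one participant, and 15% fits poorly with an event described as uncommon. The 15–43% in the Background cannot stand in for it, since that range concerns responses opposite to the group average, not failure on both wedges.

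Finally, a reader might infer that the trial falls below its stated 80% power. The documents do not support this. The power was stated for within-group comparisons, and the between-group comparisons are labelled exploratory, so two-sample power figures do not answer the question. For the paired test, the result turns on a correlation that is not given.

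**Conclusion.** The point holds as a conditional shortfall in the recruitment target. The calculation allows for one of two planned losses, has no slack for the other, and leaves open where the 46 is counted. If it is counted before the KAM check, the expected analysable number is about 38, 37, 35 or 33 against 40, at assumed exclusion rates of 2%, 5%, 10% or 15%. About one of the missing participants comes from how the dropout allowance was computed; the KAM check accounts for the rest, about 1, 2, 4 or 6.

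It is not shown that the paired test loses its 80% power. The figures of 79.0% to 73.1% hold only under the zero-correlation formula behind the 20 per group. The defect is modest, but it is specific and cheap to correct.

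**What to change.** In the abstract (Methods/design) and the Sample size calculation, state that the recruitment target counts only participants who have passed the KAM check, and that those screened out are reported separately. Reconcile the Randomization and Blinding sections so that the article gives one order for randomization and KAM check. If 46 is to remain the number consented, give the expected analysable number at a stated, assumed exclusion rate. While editing, note that dividing by 0.85 gives 48 participants past the check, where 46 falls about one short.

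The cost is a few sentences, plus either a few more people screened at baseline (for scale, about 50 to 56 recruits for 40 analysable at 5% to 15% exclusion) or a slightly less favourable stated figure.

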### Statistical analysis

Descriptive analyses will be performed on all variables. Outcome measures data will be plotted to assess trends of change over the 3 months.

#### Within group analyses

All data will be analyzed on an intention to treat basis. Changes from baseline to 3 months will be assessed within groups for ordinal data (UCLA score) using Wilcoxon Signed Rank test (α = 0.05). KOOS subsection scores and PASE scores will be compared between baseline and at 3 months using paired-samples t-tests (α = 0.05). KAMs, KAM impulse, varus thrust, and footwear comfort will be compared between the neutral shoe and assigned wedged insole condition at baseline for the KAM-R group using paired-samples t-tests (α = 0.05). All tests will be two-tailed, except in the case of KAMs and KAM impulse, where one-tailed tests will be used. The reason for this is that KAM reduction is strictly controlled in this study and so KAM and KAM impulse reductions are the only possible outcome.

A multivariable linear regression (α = 0.05) will also be conducted on the KAM-R group to evaluate whether KAM reduction, KAM impulse, varus thrust and footwear comfort can predict change in pain over 3 months. Covariates tested in these four models will include adiposity and Kellgren-Lawrence grade.

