#### KOOS

The Knee Injury and Osteoarthritis Outcomes Score (KOOS) is based on the Western Ontario and McMaster Universities (WOMAC) Arthritis Index– a survey that is both valid and reliable for measurement of pain, function and stiffness in OA populations [26–32]. Additionally, the KOOS includes subscales that can evaluate function in activities of daily living and during more rigorous activity, allowing it to be sensitive to differences in activity between individuals. The five KOOS components include: pain, symptoms, function in daily living, function in sport and recreation, and knee related quality of life. The KOOS has been extensively validated and can be used over long periods of time, allowing for possibility of long-term follow-up of the recruited patient cohort [33–37]. The KOOS will be administered at baseline, and at 1 month, 2 months and 3 months follow-up.

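### The named KOOS tests use only patients with a 3-month score unless missing scores are imputed, which fits poorly with the intention-to-treat statement, and no named test uses the month-1 and month-2 scores

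*Protocol article*

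**What the plan says.** All references are to the protocol article.

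- **Analysis basis (Within group analyses):** "All data will be analyzed on an intention to treat basis".
- **Within-group test (same section):** "KOOS subsection scores and PASE scores will be compared between baseline and at 3 months using paired-samples t-tests".
- **Between-group test (Between group analyses):** "Changes over 3 months will also be assessed between groups using a MANOVA (α = 0.05) with independent-samples t-tests for post-hoc analysis". The section labels all between-group comparisons exploratory.
- **Visits (KOOS):** "The KOOS will be administered at baseline, and at 1 month, 2 months and 3 months follow-up". The Physical activity section gives PASE the same schedule.
- **Purpose of the primary outcome, KOOS pain (Primary outcome measures):** to "identify the overall treatment effect of the wedged insole intervention over the 3-month follow-up period".
- **Only stated use that could cover months 1 and 2 (Statistical analysis):** "Outcome measures data will be plotted to assess trends of change over the 3 months".
- **Expected loss (Sample size calculation):** "To account for a potential dropout rate of 15%, we will recruit a minimum of 46 participants". The calculation is for within-group change only.

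The article gives no rule for a missing 3-month score, and it does not say that the tests are limited to patients with complete pairs.

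**The concern.** A paired t-test needs both members of the pair. A t-test on change needs the same two scores, and a MANOVA in its standard form drops any record that lacks one of the listed outcomes. Unless missing scores are filled in, a randomised patient with no 3-month survey contributes nothing to the KOOS result, even if the month-1 and month-2 surveys were returned. That sits badly with a statement that all data are analysed by intention to treat in a trial that plans for 15% loss.

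The stake is bias. If patients with little early improvement are less likely to return the last survey, the remaining patients show too large a mean change. This matters most for the within-group change in the KAM-R arm: it is a comparison the trial is sized for, and no control arm enters it to offset the error. The month-1 and month-2 scores carry information about the missing month-3 scores, and they are already being collected.

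**Working it through.** **Inputs from the article.** Target change 13.4, SD 15, two-sided alpha 0.05, power 80%, 20 per group, 40 in total, dropout 15%, 46 recruited.

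**Assumptions (not in the article).** SD 15 at every visit; equal correlation r between any two visits, r = 0.3 to 0.7; 15% of month-3 scores missing in the arm; loss depends on the change already seen at an earlier visit.

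**1. The plan's own figures.** 2 × (15 × (1.960 + 0.842) / 13.4)² = 19.67, so 20 per group and 40 in total. 40 × 1.15 = 46. Both reproduce.

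**2. Patients in the paired test.** 46 × 0.85 = 39.1, so about 39 complete pairs and about 7 patients left out.

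**3. Power is not the main problem.** With 19 to 20 pairs per group, paired t-test power is 74–76% at r = 0, 87–89% at r = 0.3 and 96–97% at r = 0.5. Unless r is near zero, the issue is who is analysed.

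**4. Bias, extreme case.** Suppose the 15% lost are exactly those with the worst month-1 change.
- SD of change = 15 × √(2(1 − r)).
- Correlation of month-1 change with month-3 change = (1 − r) / (2(1 − r)) = 0.5.
- Mean standardised month-1 change in the retained 85% = φ(1.036) / 0.85 = 0.274.
- Bias = SD of change × 0.5 × 0.274.

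| r | SD of change | Bias (points) |
|---|---|---|
| 0.3 | 17.75 | 2.4 |
| 0.6 | 13.42 | 1.84 |
| 0.7 | 11.62 | 1.6 |

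At r = 0.6 this is 1.84 / 13.4 = 14% of the target change.

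**5. Bias, moderate dependence.** With a logistic dependence of loss on month-1 change (15% lost, r = 0.6), the bias is 0.5, 0.9 and 1.2 points for log-odds slopes of 0.5, 1.0 and 1.5 per SD.

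A separate simulation used 23 per arm, a true change of 13.4, about 14% missing and loss depending on month-2 change:

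| r | All patients | Complete pairs | Difference | Estimate using months 1 and 2 |
|---|---|---|---|---|
| 0.3 | 13.38 | 14.50 | 1.1 | 13.36 |
| 0.5 | 13.39 | 14.33 | 0.9 | 13.37 |
| 0.7 | 13.46 | 14.20 | 0.7 | 13.48 |

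Using the early visits removes essentially all of the bias, because here loss depends only on observed scores. Standard errors hardly change (4.05 against 3.99, 3.33 against 3.32, 2.64 against 2.60).

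**6. Precision (r = 0.6).**
- *Month 3.* Correlation between follow-up visits after baseline adjustment = (0.6 − 0.36) / (1 − 0.36) = 0.375. Months 1 and 2 then explain R² = 2 × 0.375² / 1.375 = 0.20 of month 3. The variance reduction against completers is about 0.15 × 0.20 = 3%.
- *Average over months 1 to 3.* Variance ratio to month 3 alone = ((1 + 2 × 0.6)/3 − 0.36) / (1 − 0.36) = 0.58. It is 0.49 at r = 0.3 and 0.61 at r = 0.7.

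**The case against.** The strongest reply is that the article nowhere restricts the analysis to completers. It names a test and states intention to treat; a paired t-test can be run on imputed scores; and an imputation rule commonly sits in a full protocol or SAP that is not shown. This stands. The restriction is inferred from the test, and the missing rule is not itself an error. It does not dispose of the point, because the tests that are named would still leave two collected visits unused.

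Four stronger readings are tempting, and the article does not support them.

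- **The early scores are discarded.** Outcome data are to be plotted over the 3 months. They are outside the tests, not outside the report, and testing at one stated time point is legitimate.
- **Patients who stop wearing the insole leave the analysis.** The Adherence section records insole hours and disallowed therapies at each follow-up and has no rule that removes anyone. Only a missing 3-month survey matters.
- **Completer results favour KAM-R over control.** That needs dropout to differ between arms. The waitlist design was chosen partly for retention (Footwear insole interventions), which makes a difference conceivable, but the article gives no evidence of one. Similar loss in both arms would largely cancel in the arm comparison.
- **Sizing for dropout proves a completer analysis.** Raising 40 to 46 is routine and does not define an analysis set.

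**Conclusion.** The point holds as a poor fit between the stated basis and the named tests, together with a better method that the planned data already allow. Without imputation, about 7 of 46 patients would supply no month-3 KOOS result at the planned dropout. If those lost are doing poorly, the within-group change is too high by roughly 0.5 to 1.2 points, and by 1.6 to 2.4 points in the extreme case, against a target of 13.4. These sizes rest on an assumed SD of 15 at each visit, assumed correlations and an assumed dropout mechanism. If loss is unrelated to response, there is no bias. No figure stated in the article is shown to be wrong by this point. A reader might also infer a large precision gain from adding visits: at month 3 it is about 3%, and the ratio of 0.58 belongs only to a 3-month average. The change should be made, but the point does not invalidate the design.

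**What to change.** Replace the KOOS and PASE paired t-tests, and the MANOVA on their change scores, with a repeated-measures mixed model for each score. Include every randomised patient in the main study and all collected visits (baseline, months 1, 2 and 3), with terms for arm, visit, arm-by-visit and sex, the randomisation stratum. Report the within-arm change at month 3 and the between-arm difference at month 3 from the same model. Each keeps whatever primary or exploratory status the plan gives it; promoting the arm comparison would be a separate decision. A 3-month average can be added as a supportive estimate.

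If the sponsor prefers to keep the two-visit tests, the plan should at least say how a missing 3-month score is handled so that the intention-to-treat statement holds.

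The cost is analysis wording and standard software, with no new visits, data or patients. There is slightly more modelling in a small sample: a fully unstructured covariance over four visits has 4 × 5 / 2 = 10 parameters. The model relies on scores being missing at random given the observed visits, a weaker assumption than an analysis of complete pairs makes, but still an assumption.
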